## Abstract

**Background:**

The world has been confronted with the COVID-19 pandemic for more than one year. Severe disease is more often found among elderly people, whereas most young children and adolescents show mild symptoms or even remain asymptomatic, so that infection might be undiagnosed. Therefore, only limited epidemiological data on SARS-CoV-2 infection in children and young adults are available.

**Objective:**

This study aims to determine the prevalence of SARS-CoV-2 antibodies in children from the city of Tübingen, Germany, and to measure the incidence of new cases over 12 months.

**Methods:**

SARS-CoV-2 antibodies will be measured in saliva as a surrogate for a previous SARS-CoV-2 infection. Children will be sampled at their preschools, primary schools, and secondary schools at three time points: July 2020, October to December 2020, and April to July 2021. An adult cohort will be sampled at the same time points (ie, adult comparator group). The saliva-based SARS-CoV-2–antibody enzyme-linked immunosorbent assay will be validated using blood and saliva samples from adults with confirmed previous SARS-CoV-2 infections (ie, adult validation group).

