## Methods

### Study Design

Our study, titled Coro-Buddy (Coronavirus and Antibody Buddy), is a longitudinal, prospective, observational study to determine the prevalence of SARS-CoV-2 antibodies as a surrogate for previous infections in children and adolescents, and the change of antibody incidence over 12 months. Saliva samples from each study participant were collected at three time points: time point 1 (T1), after the release of lockdown measures in spring 2020 (ie, summer 2020); time point 2 (T2), before the winter season 2020; and time point 3 (T3), after the winter season 2021. An adult cohort (ie, adult comparator group) was sampled at the same time points to describe the seroepidemiological profile in adults. In addition, to establish and validate the SARS-CoV-2 antibody measurement process in saliva, an additional adult cohort group (ie, adult validation group) will have saliva and peripheral blood samples collected every 2 months at seven time points, over a 1-year follow-up. See Figure 1 for an overview of the study flow.

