### Questionnaire

A structured questionnaire with six questions addressing exposure to SARS-CoV-2 infection in the family was administered at each of the three time points to the parents and representatives of the children as well as to the participants in the adult comparator group (Multimedia Appendix 2).

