### Laboratory Analysis

Saliva and blood samples were processed according to standard procedures and stored at –20 °C until analysis by ELISA to identify SARS-CoV-2–reactive antibodies. A previously established and validated in-house ELISA to detect antibodies against SARS-CoV-2 in saliva was performed [20]. Blood samples from the validation group cohort will be analyzed using a certified commercial ELISA by EUROIMMUN to quantify immunoglobulin G reactive to the S1 domain of the of SARS-CoV-2 spike protein.

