## Discussion

The world was confronted with the COVID-19 pandemic, which has become the biggest public health crisis of recent times, has caused a large number of deaths, and has become a burden on intensive care facilities [2]. The majority of affected persons are older than 18 years, although adolescents and children can also become infected, with recent estimates in the range of 5% [21-23]. Different study designs can provide information on the transmission dynamics in children. Large population-wide serosurveillance studies have been performed in Europe using blood samples [11,24,25]; however, in order to facilitate large population studies in school-aged children, especially if multiple samples are collected from within the same population, saliva samples should be considered. With these factors in mind, the Coro-Buddy study was developed as a prospective, longitudinal study and will report the prevalence of SARS-CoV-2 infection in children in a sample that is representative of the study area, Tübingen, a university city in the south of Germany. The study will also be able to report on the prevalence of previous SARS-CoV-2 exposure in the different age cohorts—1 to 6 years, 7 to 10 years, and 11 to 18 years—as well as the incidence of new cases at three different time points, representing the end of school closures in Germany in summer 2020, and before and after the winter 2020-2021 period.

Children were enrolled and sampled at their respective preschools or school centers to ensure representativeness of the young population in the study area. The infection rate will be determined by measuring antibodies against SARS-CoV-2 in saliva via noninvasive sampling. This approach is particularly amenable for community studies where the significance of the outcome increases by unbiased sampling. The study will also report on a validated saliva-based SARS-CoV-2–antibody ELISA procedure that can be used in future antibody prevalence studies. In addition, the study will report on the number of SARS-CoV-2 infections per institution; this data could contribute to comparative analysis with data collected beyond this study to better understand the pandemic retrospectively.

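### At T3 (April to July 2021) antibody in saliva is still read as past infection with no described account of vaccination, so adult and possibly older-adolescent positivity may mix the two

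*Protocol article*

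**What the plan says.** The Abstract (Methods) sets the outcome rule: "SARS-CoV-2 antibodies will be measured in saliva as a surrogate for a previous SARS-CoV-2 infection". The Discussion repeats it without a time limit: "The infection rate will be determined by measuring antibodies against SARS-CoV-2 in saliva via noninvasive sampling".

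The rule covers "three time points: July 2020, October to December 2020, and April to July 2021". According to Study Design, the adult comparator group "was sampled at the same time points to describe the seroepidemiological profile in adults".

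The sections where vaccination could have been handled do not mention it:

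- **Study Population:** there is no vaccination criterion for children or for comparator adults.
- **Questionnaire:** the only description is "A structured questionnaire with six questions addressing exposure to SARS-CoV-2 infection in the family was administered", at each time point. The form itself is an appendix that is not shown.
- **Laboratory Analysis:** the saliva ELISA is attributed to a cited source and its antigen is not given. The one antigen named belongs to the commercial blood assay in the validation group, used "to quantify immunoglobulin G reactive to the S1 domain" of the spike protein.
- **Data Analyses:** prevalence will be computed and adjusted in a named R package, with no vaccination term mentioned.

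Results says that the analysis will follow the end of data collection.

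**The concern.** A rule that equates antibody with past infection works while infection is the only source of antibody. It fails once vaccination is a second source and the assay cannot tell the two apart. The article states the rule as fixed for all waves, so this is more than a detail left to a fuller document: applied literally at T3, the rule classes a vaccinated, never-infected participant with a positive sample as previously infected.

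Vaccination is unlikely to be spread evenly over the age groups. If adults are vaccinated and young children are not, the error falls on one side of the child-adult comparison and could look like a real age difference in infection. Any vaccinated participants among the oldest adolescents in the 11 to 18 stratum (n=800) would be affected in the same way. That stratum belongs to the study's main target population, and a vaccinated adolescent turning positive at T3 would be counted as a new case.

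**Working it through.** **1. The plan's own figures.** Sample Size uses 567 per 100,000 = 0.00567.

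- Adults: 400 × 0.00567 = 2.268 (stated: at least 2.2).
- Children at T1: 1850 × 0.00567 = 10.49 (stated: at least 10.4).

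Both reproduce, with truncation. The point does not rest on them, but they show how few true cases the planning rate implies and so how few misclassified participants would matter.

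**2. Inputs for the illustration.** None of these is in the document; all are assumptions.

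- p = 5% truly infected by T3
- c = vaccine coverage, 10% to 60%
- d = share of previously infected adults positive in saliva, 80% to 95%
- d_v = share of vaccinated, uninfected adults positive in saliva, set either to 0 or equal to d

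Vaccination is taken as independent of past infection, and there are no other false positives.

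**3. Formula.** Apparent prevalence A = p·d + (1 − p)·c·d_v.

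| Case | From infection | From vaccination | A | Ratio to infection alone |
|---|---|---|---|---|
| d_v = 0, d = 80% | 0.05 × 0.80 = 4.0% | 0 | 4.0% | 1 |
| d_v = 0, d = 95% | 0.05 × 0.95 = 4.75% | 0 | 4.75% | 1 |
| c = 10%, d = d_v = 80% | 4.0% | 0.95 × 0.10 × 0.80 = 7.6% | 11.6% | 2.9 |
| c = 60%, d = d_v = 95% | 4.75% | 0.95 × 0.60 × 0.95 = 54.15% | 58.9% | 12.4 |

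When d_v = d, detection cancels and the ratio is 1 + (1 − p)·c/p: 1 + 0.95 × 0.10/0.05 = 2.9 and 1 + 0.95 × 0.60/0.05 = 12.4. The full range therefore starts at 1 (no effect).

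**4. Low coverage at the planning rate.** Take p = 0.00567, every infection detected, 5% coverage and half of vaccinees positive.

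- A = 0.00567 + 0.99433 × 0.05 × 0.5 = 0.0305.
- In the planned 400 adults this is 12.2 positives instead of 2.3, an excess of 9.9. About 81% of positives would reflect vaccination.

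If 1850 children, none vaccinated, were compared with 400 adults at two-sided 0.05, with equal true prevalence and independent participants, the chance of a spurious difference would be about 94%. At 1% coverage with half positive it would be about 24%. At an assumed 5% infected, 10% coverage and half positive, it would be about 92%. The article specifies no such test; these figures only show how readily a false contrast could appear.

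**The case against.** The case on the other side is substantial, and much of it stands.

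- **The mechanism is conditional.** The article does not say that anyone was vaccinated by T3, and the saliva antigen is left to a cited source. The spike S1 assay is used on validation-group blood and does not classify comparator adults. If the saliva read-out does not respond to vaccination, the excess is zero.
- **Vaccination status may have been recorded.** The questionnaire appendix and the case report form are not shown. The description of the six questions does not say that they cover nothing else.
- **The stated objective concerns children.** The adult group is there to describe adult antibody status, and that description remains correct as a statement about antibody.
- **Analysis rules are often left to fuller documents.** This is true of how vaccinees are excluded or stratified.

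A reader might go further and infer that an adult T2 to T3 incidence, a formal child-adult test, or late assay sensitivity in the validation group is already wrong. The documents do not support this, because none of these analyses is specified. Validation participants all had confirmed earlier infection, so vaccination creates no false cases there. It could only mask a decline in antibody, and that matters only if late visits are used to estimate sensitivity.

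What the objection does not remove is the outcome rule itself. The article states it for every wave, with no condition at T3 and no statement that the assay is unaffected by vaccination. The approved amendment for blood from antibody-positive children at T3 (Results) does not close the gap either: the article does not say what that blood will be tested for, and the amendment does not reach adults.

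**Conclusion.** The point holds in a conditional form. Under two assumptions outside the document (vaccination under way by T3, and a saliva read-out that responds to vaccine-induced antibody), T3 positivity cannot be read as past infection in the adult comparator group or in any vaccinated older adolescents, and a descriptive child-adult comparison at T3 would mislead. T1 is unaffected and young children are not directly affected.

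The size is open, from no excess to the 12% and 59% of the illustration. It would be tempting to report a 3- to 12-fold overstatement in 560 adults. The document does not support that: the range leaves out the no-effect case, coverage and detection are assumed, and 560 is the number enrolled, while the number sampled at T3 is not given. Nor does the point show that the children's main prevalence estimates are invalid.

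**What to change.** Before the pending analysis:

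1. State whether the saliva read-out detects vaccine-induced antibody. If it does not, one sentence saying so settles the saliva question.
2. Otherwise, establish vaccination status and first-dose date at T3 for comparator adults and vaccine-eligible adolescents, from existing forms or by call-back.
3. Report T3 infection prevalence and new cases among participants unvaccinated at sampling. Count a vaccinated person as infected only on a positive sample taken before vaccination, a reported PCR, or an antibody that vaccination does not induce.
4. Report overall antibody prevalence separately and label it as such.
5. If validation-group visits are used to estimate assay sensitivity, use only visits before the first dose.

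The cost is one data item or a call-back and one analysis rule. The adult T3 denominator shrinks, and those still unvaccinated are a selected group; the report should say both.

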**Results:**

The first study participant was enrolled in July 2020, and recruitment and enrollment continued until July 2021. We have recruited and enrolled 1850 children, 560 adults for the comparator group, and 83 adults for the validation group. We have collected samples from the children and the adults for the comparator group at the three time points. We followed up with participants in the adult validation group every 2 months and, as of the writing of this paper, we were at time point 7. We will conduct data analysis after the data collection period.

**Conclusions:**

Infection rates in children are commonly underreported due to a lack of polymerase chain reaction testing. This study will report on the prevalence of SARS-CoV-2 infections in infants, school children, and adolescents as well as the incidence change over 12 months in the city of Tübingen, Germany. The saliva sampling approach for SARS-CoV-2–antibody measurement allows for a unique, representative, population-based sample collection process.

**Trial Registration:**

ClinicalTrials.gov NCT04581889; https://clinicaltrials.gov/ct2/show/NCT04581889

**International Registered Report Identifier (IRRID):**

DERR1-10.2196/27739

## Introduction

The end of 2019 was marked by the emergence of a novel betacoronavirus, called SARS-CoV-2, which caused an outbreak in the Chinese city of Wuhan [1] and eventually spread to more than 180 countries. On March 11, 2020, the World Health Organization declared the COVID-19 outbreak a global pandemic [2,3]. The novel virus spreads rapidly by efficient human-to-human airborne transmission [4]. Symptoms mainly include fever, cough, myalgia, loss of smell or taste, and a severe manifestation of pneumonia, but other symptoms of respiratory tract infections can also occur [5-7]. Children infected with SARS-CoV-2 typically experience mild disease or are asymptomatic [8]; few pediatric cases of severe or fatal COVID-19 have been reported [7]. In Germany, a total of 3,756,497 laboratory-confirmed SARS-CoV-2 infections, including 117,482 deaths, have been recorded as of July 2021 by the Robert Koch Institute in Berlin, Germany [9]. Among those, 225,270 were children under 10 years of age (6.0%) and 366,472 (9.8%) were adolescents aged 10 to 19 years [9]. At the time, the diagnostic strategy focused primarily on testing symptomatic individuals, and children may have been underrepresented in such records. Also, hospital-based studies or case series are biased toward recruitment of a selected group, and the fraction of identified children infected with SARS-CoV-2 is not generalizable to the larger population [10].

Epidemiologic surveys require an unbiased, sufficiently large, representative sampling approach. Screening for SARS-CoV-2–reactive antibodies allows for the retrospective identification of virus exposure and is amenable to large cohorts [11]. However, the prerequisite of blood sampling [12] is a hurdle to the screening of large pediatric cohorts, particularly outside of the medical context. Interestingly, antibodies are also secreted by mucosal tissues, and SARS-CoV-2–specific antibodies can be detected in saliva and other body fluids [13]. Saliva sampling as a noninvasive method (ie, it does not cause disturbance) for SARS-CoV-2 antibody measurements and is an elegant approach to rapidly assess the prevalence of SARS-CoV-2 infection in vulnerable cohorts at numbers appropriate for epidemiologic investigations [14]. Studies have reported the use of saliva not only for detection of respiratory viruses, including coronaviruses and SARS-CoV-2 [15], but also for detection of antibodies against measles, rubella, mumps, and hepatitis [16-18]. The number of seroprevalence studies benefiting from noninvasive saliva sampling is increasing [19].

This study assesses the prevalence of SARS-CoV-2 antibodies as a surrogate for previous infections in children (aged 1-18 years) and measures the change of incidence over a 12-month period in a defined study area. The study takes place in Tübingen, a middle-sized university city in the Federal State Baden-Württemberg, Germany. Saliva samples from children were collected three times in preschools, primary schools, and secondary schools: summer 2020, 6 months later, and 12 months later (ie, before and after winter 2020-2021). SARS-CoV-2 antibodies will be measured in-house using a pre-established enzyme-linked immunosorbent assay (ELISA).

## Methods

### Study Design

Our study, titled Coro-Buddy (Coronavirus and Antibody Buddy), is a longitudinal, prospective, observational study to determine the prevalence of SARS-CoV-2 antibodies as a surrogate for previous infections in children and adolescents, and the change of antibody incidence over 12 months. Saliva samples from each study participant were collected at three time points: time point 1 (T1), after the release of lockdown measures in spring 2020 (ie, summer 2020); time point 2 (T2), before the winter season 2020; and time point 3 (T3), after the winter season 2021. An adult cohort (ie, adult comparator group) was sampled at the same time points to describe the seroepidemiological profile in adults. In addition, to establish and validate the SARS-CoV-2 antibody measurement process in saliva, an additional adult cohort group (ie, adult validation group) will have saliva and peripheral blood samples collected every 2 months at seven time points, over a 1-year follow-up. See Figure 1 for an overview of the study flow.

**Figure 1 figure1:**
[figure not shown]
Study flowchart for participant sampling. T: time point.

### Study Population

Children and adolescents were enrolled and sampled via preschools, primary schools, and secondary schools randomly spread over the Tübingen city area. In total, 1850 children and adolescents were enrolled: (1) preschools—infants aged 1 to 3 years (n=350) and young children aged 4 to 6 years (n=350), (1) primary schools—children aged 7 to 10 years (n=350), and (3) secondary schools—children and adolescents aged 11 to 18 years (n=800). Study participants and their families were informed about the study and its aims via their institutions. In addition to all relevant documents, families were also provided with a link to a video that explains the study (Multimedia Appendix 1) and procedures in an easy-to-understand way to ensure broad participation. Saliva was sampled after written informed consent has been given by parents or legal representatives. Assent from children aged 12 years and older was collected on the day of first sampling. Inclusion criteria include the following: aged 1 to 18 years, enrolled in an educational institution within the city of Tübingen, and written informed consent given or written assent given if the child is 12 years or older. Exclusion criteria include not attending a preschool or school in the city of Tübingen.

For the adult comparator group (n=400), any person aged 18 years and older living or working in Tübingen who had given written informed consent could be enrolled. For the adult validation group (n=40), the following individuals can participate in the study: those with a previous SARS-CoV-2 infection, confirmed by either quantitative polymerase chain reaction or by ELISA with a SARS-CoV-2–specific antibody at any time period before enrollment, who have given written informed consent. Blood and saliva samples are being collected every 2 months for 12 months (Figure 1).

### Sample Size

Tübingen has a total of 91,656 inhabitants; among them, 4910 are children under the age of 6 years and 8366 are children between the ages of 6 and 18 years (≤6 years: n=4061; 7-18 years: n=6621, as of December 31, 2019). Therefore, in total, 13,276 children were living in Tübingen at the time of the study; of these, we aimed to recruit 1850 children and young adults. In addition, 400 adults will be included as an adult comparator group. At the time of planning, 567 out of 100,000 inhabitants—as determined by the Robert Koch Institute in Berlin, Germany, on June 1, 2020—have had a confirmed SARS-CoV-2 infection in the county of Tübingen, but the number of unreported and asymptomatic infections is believed to be higher. Therefore, we expect to have at least 2.2 positive cases in the adult group; in the event that children are infected at an equal frequency, we expect to find at least 10.4 positive cases in children at T1.

### Questionnaire

A structured questionnaire with six questions addressing exposure to SARS-CoV-2 infection in the family was administered at each of the three time points to the parents and representatives of the children as well as to the participants in the adult comparator group (Multimedia Appendix 2).

### Saliva and Blood Collection

Saliva samples were collected from children 6 years and below using an ORACOL S14 saliva collection device (Malvern Medical Developments) by gently brushing the gumline for 2 minutes. For children 7 years and above, 3 mL of saliva was collected by spitting into a plastic tube; 30-mL multipurpose containers (item No. 201150; Greiner Bio-One) were used for this purpose. Saliva samples were kept on ice for a maximum of 3 hours before further processing. The ORACOL S14 saliva collection device was centrifuged at 2500 rpm for 10 minutes and the 30-mL multipurpose containers were centrifuged for 6 minutes. Supernatant was transferred into a 2-mL microtube and inactivated using a solvent and detergent treatment to a final concentration of 0.3% tri-*n*-butyl phosphate and 1% Triton X-100. Samples were immediately stored at –20 °C. Blood was collected by vein puncture into 9-mL lithium-heparin Monovettes; the plasma was obtained by centrifugation at 1400 rpm for 10 minutes and stored at –20 °C.

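### Specimen type changes at the 6/7-year line that also separates the first reported age cohort, so prevalence in 1-6 years versus either older cohort cannot separate age from device

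*Protocol article*

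**What the plan says.** In the protocol article, Saliva and Blood Collection gives two procedures. For the younger group, "Saliva samples were collected from children 6 years and below using an ORACOL S14 saliva collection device", by brushing the gumline for 2 minutes. For the older group, "For children 7 years and above, 3 mL of saliva was collected by spitting into a plastic tube". Processing also differs: the ORACOL device is "centrifuged at 2500 rpm for 10 minutes and the 30-mL multipurpose containers were centrifuged for 6 minutes", with no speed given for the containers.

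The Discussion says that the study will report "the prevalence of previous SARS-CoV-2 exposure in the different age cohorts", which it lists as "1 to 6 years, 7 to 10 years, and 11 to 18 years". Study Population gives the enrolled numbers: 350 aged 1-3, 350 aged 4-6, 350 aged 7-10 and 800 aged 11-18. Study Design has every participant sampled at T1, T2 and T3, and the Objective includes incidence of new cases over 12 months.

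Laboratory Analysis names one in-house saliva ELISA. The Abstract describes its validation in adults with confirmed past infection; their saliva device is not stated. Data Analyses says that prevalence will be adjusted with epiR and does not mention device.

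**The concern.** Brushed gumline fluid and spat saliva are different specimens with different handling, and they may differ in antibody yield or background signal. If they do, the same true prevalence gives different positivity on the two sides of age 7. Because the reporting cohorts are cut at the same age, that difference would look like an age effect. The pooled child prevalence also mixes the two specimens, with 700 of 1850 children (38%) brushed at T1.

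The longitudinal objective is exposed as well. If a child moves from brushing to spitting between rounds, a change in assay performance can pass for seroconversion or for loss of antibody. With few true new infections, a few such changes could matter.

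**Working it through.** **Check on the plan's own figures.** Sample Size uses 567 per 100,000. Adults: 400 × 0.00567 = 2.27 (stated 2.2). Children: 1850 × 0.00567 = 10.49 (stated 10.4). Both reproduce, apparently truncated.

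**Cohort by device at T1** (Study Population numbers, Saliva and Blood Collection rule):

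| Cohort | Brushed | Spat |
|---|---|---|
| 1-6 years | 350 + 350 = 700 | 0 |
| 7-10 years | 0 | 350 |
| 11-18 years | 0 | 800 |

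No cohort contains both devices. Two of the three pairwise contrasts (1-6 with 7-10, and 1-6 with 11-18) are collinear with device. The third (7-10 with 11-18) uses spat saliva on both sides.

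**Expected true positives by device at the planning rate.** Brushed: 700 × 0.00567 = 3.97. Spat: 1150 × 0.00567 = 6.52.

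**Size of a possible device effect.** The documents give no device-specific sensitivity (Se) or specificity (Sp), so every Se and Sp value below is assumed. Apparent prevalence = prev × Se + (1 − prev) × (1 − Sp), with the same true prevalence in both groups and spat saliva at Se 0.90, Sp 1.00.

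- Specificity gap of 1 point: false positives among brushed children = 700 × (1 − 0.00567) × 0.01 = 6.96, about 7 against 4 expected true cases. With Se 0.90 for both devices, apparent prevalence is 0.00567 × 0.90 + 0.99433 × 0.01 = 0.0150 brushed and 0.00567 × 0.90 = 0.0051 spat, a ratio of 2.95. The pooled child figure rises by 6.96/1850 = 0.38 percentage points.
- Sensitivity gap with Sp 1.00 for both: the young/older ratio is 0.80/0.90 = 0.89, 0.70/0.90 = 0.78 or 0.60/0.90 = 0.67, whatever the prevalence. A correction using one common Se divides both sides by the same number and leaves the ratio unchanged.
- Chance of a spurious two-sided p < 0.05 (700 versus 1150) with those three sensitivities: about 11%, 32% and 65% at an assumed 10% prevalence; 7%, 17% and 36% at 5%; no more than 7% at 0.567%. The article states no such test, so this only shows scale.
- The two gaps can offset each other: at 5% prevalence, brushed Se 0.70 with Sp 0.99 gives a ratio of 0.99. The direction of any distortion is therefore not known in advance.

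Specificity is thus the main exposure at T1, and sensitivity matters more as prevalence rises.

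**Possible switchers.** Assume ages are even within the 4-6 band, no dropout, and device set by age at each visit. July 2020 to April-July 2021 is 9 to 12 months. Number passing their seventh birthday: 350/3 × 9/12 = 87.5 to 350/3 × 12/12 = 116.7, or about 88 to 117. That is 12.5-16.7% of the 700 brushed children and 4.7-6.3% of all 1850.

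**The case against.** Much can be said on the other side. Collecting saliva differently from very young children is a reasonable feasibility choice in a cohort that starts at age 1. The article undertakes to report prevalence by cohort with descriptive statistics and names no between-cohort test. The adjustment inputs may be set out in an analysis plan that is not shown, and the assay is described as validated in earlier work that cannot be consulted here.

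These points limit the finding. A reader might infer four stronger things that the documents do not support:

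- That every age comparison is confounded. It is not: 7-10 and 11-18 years share one device.
- That one common Se/Sp correction will be applied to all ages. Data Analyses does not say this, and its silence is no commitment.
- That children certainly change device in mid-study. The article does not say whether age at enrolment or age at the visit governs; under enrolment age nobody switches.
- That the results are biased. Collinearity shows that a device effect could not be told apart from age, not that one exists.

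The alignment of the two boundaries still stands, and the article fixes it itself. Three cohort figures reported together will be read across the 6/7 line whether or not a test is run. An adjustment removes a device effect only if its accuracy inputs are device-specific, and no data source described supplies them fully. The validation group, as described, consists of previously infected adults with no stated saliva device. The T3 blood samples come only from antibody-positive children.

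**Conclusion.** The point holds for readings across the 6/7-year line and, to a lesser degree, for the pooled child prevalence. It should be fixed; it does not undermine the study as a whole. The collinearity follows directly from the stated device rule and cohorts and needs no assumption. Its consequences do rest on assumptions: a 1-point specificity gap would add about 7 false positives to about 4 expected true ones at T1, and sensitivity of 60-80% against 90% would give a ratio of 0.67-0.89 with no true age difference. The count of 88-117 switchers depends on device following age at each visit, even ages within 4-6 years and no dropout.

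**What to change.** 1. State whether age at enrolment or age at each visit governs the device, and carry device as a variable for every sample. Data Management does not say that it is recorded; once the rule is stated, it can be derived from age and sampling date.
2. Make age comparisons within device: 1-3 versus 4-6 years, and 7-10 versus 11-18 years.
3. Present 1-6 versus older, and the pooled child prevalence, with a sensitivity analysis over a stated range of device-specific Se and Sp. T1 positivity by device helps to set the specificity range: as long as Se + Sp exceeds 1, 1 − Sp cannot exceed apparent positivity, apart from sampling error. The T3 blood samples inform positive predictive value only, not sensitivity, so the sensitivity range has to be assumed and declared as such.
4. Flag children whose device changed, and report the seroconversion count with and without those transitions.

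The cost is analysis wording, one derived variable and a few extra tables. Analysis had not begun when the article was written, so this can be fixed before results are seen. The price is a weaker claim across 6/7 and a slightly smaller seroconversion set in the sensitivity analysis. Measuring brushed-sample sensitivity would need paired or reference samples; the article describes none, and all three rounds of child sampling are already complete.
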